# Evaluating the implementation of the active life improving health behavior change program “BCP-VAMOS” in primary health care: Protocol of a pragmatic randomized controlled trial using the RE-AIM and CFIR frameworks

**DOI:** 10.3389/fpubh.2022.726021

**Published:** 2022-09-12

**Keywords:** Implementation Science, protocol study, program evaluation, public health, care innovation

## Abstract

**Introduction:**

The effective translation of evidence-based interventions has contributed to implementing actions that impact public policies and the population's health. However, there is a gap in the literature regarding the factors associated with the successful implementation of these interventions. The Active Life Improving Health Behavior Change Program (BCP-VAMOS) uses behavioral strategies to promote an active and healthy lifestyle in the community. Characterized as a health innovation, it also provides health professionals with online training to implement the program in Primary Health Care (PHC). Our study describes a pragmatic trial that aims to evaluate the implementation of BCP-VAMOS, version 3.0, in PHC in southern Brazil.

**Methods and analysis:**

A pragmatic randomized controlled trial (PRCT) of two arms comparing a group of PHC professionals who will participate in a traditional didactic approach (control group) vs. a group that will receive ongoing support (intervention group) for the implementation of BCP-VAMOS. The intervention will be available to adults (≥18 years old) registered at PHC. Program recipient's will be assessed at baseline and post-intervention (9 months after) to measure markers of physical activity and eating behavior (primary outcomes). Program's implementation process will be monitored for 12 months and will be evaluated using the RE-AIM and Consolidated Framework for Implementation Research (CFIR) frameworks.

**Discussions:**

The survey findings can be used widely throughout Brazil, guiding the work of health professionals, service planners and policy-makers. Also, the results may help to inform the national health promotion policy to plan interventions and improve the implementation of programs in PHC. This research results will provide practical guidance for researchers to develop similar protocols to implement and adapt public health interventions.

**Ethics and dissemination:**

Ethics approval has been granted by the Human Research Ethics Committee of the Federal University of Santa Catarina (UFSC), Brazil, under no. 1394492. Results will be published in full as open access in the UFSC library and main trial results and associated papers in high-impact peer-reviewed journals.

**Trial registration number:**

RBR-2vw77q—Brazilian Registry of Clinical Trials – ReBEC (http://www.ensaiosclinicos.gov.br).

## Introduction

Since the publication of global strategies to promote physical activity, healthy eating, and risk prevention associated with lifestyle behaviors (1), evidence-based practices (EBPs) have contributed to the implementation of public health interventions (2). In this context, a concern has arisen regarding whether these interventions are implemented as intended, and are able to promote the expected impact on the population's health (3).

Many dissemination and implementation (D&I) models, theories, and frameworks (4, 5) are available to help understanding this process. However, there is a gap in the literature concerning the implementation and adaptation of EBPs in certain contexts (6, 7). Practical implications usually include the utilization of strategies to increase adoption rates among health professionals and adapt protocols to local needs (7, 8). Nevertheless, despite the notable advance in Implementation Science (IS), the complexity that characterizes translational processes is sometimes ignored, limiting the understanding of the real effects of interventions (9).

The implementation facilitation strategies, as they deal with facing barriers to the adoption of EBPs, assist in the translational process, identifying how practices and providers can adopt and maintain interventions (4, 10, 11). The most used facilitation method includes providing didactic training for health professionals with protocols and tools to implement an intervention (12, 13). However, this strategy has been insufficient to promote widespread adoption and ineffective when it comes to the success of the implementation (11, 13). Combining traditional didactic approaches with ongoing support seems to improve the effect size of the strategies used in the intervention (14, 15). Adopting the action planning model as ongoing support after the training has effectively changed behavior, as it takes barriers and contingencies into account during the implementation of innovative practice in the health area (16).

Ongoing support improves the provider's adherence to EBPs and the quality of health services implementation. Nevertheless, further research is needed to identify effective strategies and how ongoing support affects the process and results of implementation (15). This research proposes to evaluate the impact of online training with ongoing support centered on the action planning approach and to compare it with the traditional didactic approach in the implementation of an intervention.

One way of understanding the mechanisms involved in implementation is the use of pragmatic trials with random assignment in “real world” settings (9, 17). They are designed precisely to inform decision-makers in practice (2), to report what actually works in a particular context (18), and to provide results concerning the feasibility and sustainability of interventions (19).

In light of this, we suggest a pragmatic trial to evaluate the implementation of the Behavior Change Program called Active Life Improving Health (BCP-VAMOS), which aims to motivate adults and elderly living in the community to adopt an active and healthy lifestyle (20). Online training will be available to health professionals as an adaptation strategy to assist in the implementation of the protocol (21).

The trial will be supported by RE-AIM (Reach, Effectiveness, Adoption, Implementation, Maintenance) (22) and CFIR (Consolidated Framework for Implementation Research) (23) to understand the factors involved in the implementation. Both frameworks are based on theories related to the adoption, implementation, and maintenance of EBPs (24, 25). Their combined use enables to measure success and to evaluate the factors that explain and improve implementation outcomes (26). Therefore, this study aims to describe the design and methods of a pragmatic trial that intends to evaluate the implementation of BCP-VAMOS, version 3.0, in Primary Health Care (PHC).

## Methods and analysis

### Study design

A pragmatic randomized controlled trial (PRCT) will be carried out to evaluate the implementation of BCP-VAMOS, version 3.0, in PHC (see Figure 1). The design was classified by the PRECIS-II tool (PRagmatic-Explanatory Continuum Indicator Summary) (27) and described following the SPIRIT 13 checklist (Standard Protocol Items: Recommendations for Interventional Trial), as it is the description of a study protocol that provides health outcomes (28). This research is part of the community-based trial entitled “VAMOS Program—Active Life Improving Health.” It was approved by the Human Research Ethics Committee of the Federal University of Santa Catarina, Brazil, under no. 1394492, and registered in ReBEC—Brazilian Registry of Clinical Trials (http://www.ensaiosclinicos.gov.br/) using the RBR-2VW77Q indicator on 20 July 2019. Any changes to the protocol will be registered in ReBEC.

**Figure 1 F1:**
[figure not shown]
Flow chart of procedures of the pragmatic randomized controlled trial (PRPT) for the implementation of the Active Life Improving Health Behavior Change Program (BCP-VAMOS), version 3.0, in Primary Health Care, Brazil. PHC, Primary Health Care; R, randomization; CCT+APAG, consultee-centered training plus action planning approach group; TDAG, traditional didactic approach group. ^a^The reach (R), effectiveness (E), and maintenance (M) dimensions will be considered to evaluate the impact in the implementation process between the two groups, CCT^+^APA vs. TDA. ^b^Consolidated Framework for Implementation Research.

### Description of BCP-VAMOS

Active Life Improving Health (VAMOS) is a behavior change program that aims to motivate adults and elderly (18 or older) individuals to adopt an active and healthy lifestyle through physical activity and healthy eating (20). In the current version (3.0), the face-to-face modality is developed to be implemented over 9 months in 18 sections. These sections are scheduled to be delivered weekly, biweekly and/or monthly. Each section is taught with a duration of up to 2 h, conducted by a PHC professional whose methodology is health education. The didactic material consists of 18 printed notebooks that address topics related to the benefits of physical activity and healthy eating, in addition to the development of strategies to effect and maintain new life habits (see Figure 2) (29).

**Figure 2 F2:**
[figure not shown]
Sections and themes of BCP-VAMOS, version 3.0. Brazil. Adapted from Benedetti et al. (29). The didactic material is free of charge and is distributed to participants in each of the sections. PA, physical activity; HE, healthy eating.

### Study location and participants

The study will be conducted with professionals from health teams that work in PHC in the state of Santa Catarina, southern Brazil. The state has 295 municipalities and an estimated population of 7,250,000 inhabitants. It is the third state in the national human development index (HDI = 0.774), has the lowest social inequality index (GINI = 0.494) and the highest performance index of the unique health system in the country (IDSUS = 6–6.99). PHC in Santa Catarina is divided into seven regions, with 1,824 primary care centers, 1,855 family health teams, 234 primary care teams (doctor, nurse, dentist), and 301 multidisciplinary teams (nutritionist, pharmacist, physiotherapist, physical education professional, psychologist, social worker). These teams take into consideration the multi-professional health care policy and are formed by 7,056 PHC professionals with bachelor's degree (30). As the VAMOS program in the face-to-face version requires a minimum of 8 people to start a group and we expect that around 45 health professionals can complete the training, a total of at least 360 adults may be recruited to participate in the program.

### Description of the study design

The study design is based on strategies recommended by experts (4, 31, 32), centered on organizational support (14), to assist in the fidelity of the implementation and delivery of the BCP-VAMOS. Online training was developed, and educational material was prepared in electronic and printed forms to be distributed, free of charge, to health professionals and program participants. In addition, ongoing support will be structured based on information about facilitation (problem-solving and barriers) and adaptability (fidelity) of the implementation protocol (14, 16). This support will be delivered by a specialist researcher at the PHC. Therefore, PHC professionals will be allocated into two groups to assess the impact of the program's implementation: (1) control group (CG), with PHC professionals who will participate in a traditional didactic approach without ongoing support, and (2) intervention group (IG), with consultee-centered training plus action planning approach.

$$\begin{array}{l} \begin{array}{l} CG=Traditional\;Didactic\;Approach\;(TDA) \end{array} \end{array}$$

This group will attend a 20-h online training (see Figure 3) and receive teaching materials with information and content related to the program's implementation protocol, recruitment, retention, and evaluation of participants (Table 1). The online training follows a didactic model with self-instructional language and will be made available free of charge in the e-learning modality, with the purpose to train PHC professionals (called facilitators) to plan, conduct and evaluate the program in different contexts. The online training has five modules that include themes and contents divided into 13 chapters. The content is so that the PHC professional learns about the program's proposal, the concepts and markers for behavior change, strategies for managing groups of people, the structure and content for implementation, and finally, the program's evaluation forms (see Figure 3) (21). PHC professionals must present a performance of at least 80% in the final evaluation—It is a 30-question multiple-choice quiz—to be certified as a BCP-VAMOS facilitator. The online training was developed by the BCP-VAMOS researchers' team and validated by an expert panel composed of researchers from related fields and PHC professionals (21).

$$\begin{array}{l} IG=Consultee-Centered\;Training\\ \;Plus\;Action\;Planning\;Approach\;(CCT+APA) \end{array}$$

**Figure 3 F3:**
[figure not shown]
Online training learning modules for implementation of BCP-VAMOS, version 3.0. Brazil. Adapted from Konrad et al. (21).

**Table 1 T1:** Description of strategies for groups with and without ongoing support for the implementation of BCP-VAMOS, version 3.0. Brazil.

**Intervention stage**	**Traditional didactic approach group^a^**	**Consultee-centered training + action planning approach group^b^**
**Program dissemination, participants enrollment**	Printed material to publicize and recruit the community: posters, flyers, and business cards.	Printed material plus guidelines to optimize dissemination and recruitment: who, where, when, and how.
**Program sections** (18 sections)	T-shirt with program logo for the provider. Digital guidelines, printed material to conduct the sections, record the frequency, and monitor and evaluate the sections.	T-shirt, manual, printed material plus guidelines for each of the sections: preparation of the site, reception, content guiding, participation registration, and individual section monitoring.
**Participants evaluation** (baseline and post-intervention)	Digital guidelines, video, and printed material to record the participants' baseline and post-intervention assessment data.	Digital guidelines, video, printed material plus guidelines for carrying out evaluations about: location, professionals involved, and the necessary care for reliable measures.

^a^20-h online training (21) + teaching materials. ^b^20-h online training (21)+ teaching materials + structured messages throughout the implementation process.

This group will participate in the 20-h online training as described above and will receive ongoing support centered on the provider, using an action planning strategy. Ongoing support (see Table 1) will be structured by a specialist PHC researcher and provided during 12 months for all the implementation stages: recruiting the community, conducting program sessions, and evaluating participants. Support will focus on the process of identifying barriers to program implementation, selecting strategies to deal with barriers and goals for recruiting and retaining new participants. Before the start of each stage, the intervention provider will receive a message reinforcing the strategy that should be used. After each stage, another contact will be made to assess the used strategy and provide new feedback. Support will be delivered through interviews with the provider using a smartphone messaging app.

Both groups will be monitored simultaneously. If the CG providers have questions during the implementation process, these will be answered at their origin, but, being careful not to offer strategies similar like those IG will be offered. Thus, both groups will be monitored by one single researcher to avoid communication bias and to ensure that information from the IG is not passed on to the CG. This researcher will be a specialist in the health area, particularly in PHC, and received training to implement the BCP-VAMOS.

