### New description

The randomization and allocation of health professionals into the two groups (CCT + APA vs. TDA) will be performed after all PHC professionals complete the online training. Through a randomly generated computer sequence, we will randomize each facility to one of the intervention arms with all eligible professionals within each facility randomized to the same intervention arm to avoid cross-contamination within the same facility. However, multiple facilities within the same city may be randomized to different groups. After randomization, they will be asked to implement BCP-VAMOS in their workplaces. The randomization and assignment of groups will be under the responsibility of a single researcher and will be blind to the others involved in the implementation strategies and data collection.

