To reach the participants (recruitment), we will make available printed materials (posters, folders) and we will suggest the use of social networks, in addition to the media (radio, television, internet) to publicize the program. We recommend employing these strategies during the 30-day period prior to the start of the program. In order to recruit participants, we will establish the following eligibility criteria: being 18 years of age or older, being registered and having been attended at UBS in the 30 days prior to the start of the program (30 days from the disclosure), not meeting the minimum recommendations of PA practice (150 min per week of moderate and/or vigorous PA) and/or having inappropriate eating behavior and/or being overweight/obese and/or non-communicable chronic diseases. We will provide a questionnaire (33) and guidelines (https://vamos.ufsc.br/orientacoes-para-questionario-vamos/) to PHC professionals to screen participants. This screening will be carried out through a meeting scheduled prior to the start of the program with interested users. At this meeting, in addition to screening assessments, PHC professionals will be recommended to clarify the objectives and methodology of the program. In addition, we will assess the reasons for participants' absences and dropouts throughout the program. For this, we use the PHC professionals' monitoring records (attendance list and replacement of the sections), which will be guided to record the date and reason for the termination of each participant.

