**Effectiveness**, assessed at the individual level, refers to the extent of the intervention's impact on the primary outcomes, how it changes behavior and affects the quality of life, and whether or not there are unintended results (positive or negative) (22). In this study, effectiveness will be assessed considering the primary outcomes of BCP-VAMOS: physical activity and eating behavior. Physical activity will be assessed through a self-report of the weekly practice (type, frequency, and duration) (34) and by accelerometry (35), which allows measuring the time spent on sedentary behavior, light, moderate, and vigorous physical activity. Eating behavior will be assessed through the habit and frequency of consumption of foods classified as healthy (fruits, greens, and raw or cooked vegetables) and unhealthy (sweets, snacks, and sugary drinks) (34). These data will be collected by the PHC professionals through a validated questionnaire for the BMC-VAMOS program (33). The effectiveness outcomes will be analyzed by PHC professional (staff level) to assess the impact of intervention strategies, comparing the IG to the CG.

**Adoption** is a measure at the organizational level of participation that refers to the representativeness of locations and/or agents who are willing to implement an intervention, considering those who are eligible (22). In this study, the number, proportion, and representativeness of local/PHC professionals who initiate the program delivery will be calculated using those certified by the online training with eligibility criteria. We will calculated the adoption rate by considering the ratio between the number of PHC professionals who initiated the implementation of the program in each UBS and the number of PHC professionals certified by the online training, multiplied by 100. To identify the factors that will influence the program adoption and non-adoption, qualitative data will be collected through interviews with PHC professionals.

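### Participants are enrolled after facility allocation, with recruitment support that differs by arm, so the unadjusted between-arm comparison of behavior change can mix the effect of support with differences in who was enrolled

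*Protocol article*

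**What the plan says.** **Order of events.** Under New description, allocation "will be performed after all PHC professionals complete the online training", and "we will randomize each facility to one of the intervention arms". Then: "After randomization, they will be asked to implement BCP-VAMOS in their workplaces". The Reach text in Outcomes evaluation places publicity after that: "We recommend employing these strategies during the 30-day period prior to the start of the program". It also gives a questionnaire and guidelines "to PHC professionals to screen participants", so the allocated professionals do the screening.

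**Recruitment support.** In Table 1 (dissemination and enrollment row) the control group has "Printed material to publicize and recruit the community: posters, flyers, and business cards". The intervention group has "Printed material plus guidelines to optimize dissemination and recruitment: who, where, when, and how". Description of the study design adds that ongoing support covers the recruitment stage, includes goals for recruiting and retaining participants, and brings a message before each stage and feedback after it. Similar strategies are to be kept from control providers. The same section gives both groups the 20-hour training and teaching materials, which include recruitment content.

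**Comparison.** Table 2 defines effectiveness as the proportion of participants who show a behavior change. The Effectiveness text states: "The effectiveness outcomes will be analyzed by PHC professional (staff level) to assess the impact of intervention strategies, comparing the IG to the CG". Data analysis names a t test or Mann-Whitney test for changes between groups, and Fisher's exact and chi-square tests for group characteristics. No baseline adjustment is stated.

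**The concern.** The facilities are randomized; the participants are not. They are found and enrolled after allocation, by providers whose recruitment help depends on the arm. The plan compares recruitment and participation rates between arms, so it treats enrollment as something that support may change. Effectiveness is then measured only in those who enrolled, which conditions on something that happens after randomization.

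Eligibility leaves room for case mix to differ. Its behavioral and health criteria are joined by and/or, so a person who already meets the activity recommendation can enter because of overweight or chronic disease. Such a person has less room to show an activity change than an inactive one. The proportion who change, and the mean change, then depend on who was enrolled as well as on what support did. Physical activity and eating behavior are the named primary outcomes, so this affects the causal reading of the main participant-level result.

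**Working it through.** **1. The plan's own figure.** Study location and participants expects about 45 professionals and at least 8 people per group: 45 × 8 = 360, which reproduces the stated minimum. The article gives no change rates, standard deviations or correlations, so everything below is illustration. Assumed throughout: 1:1 allocation (360 / 2 = 180 per arm), a two-sided 5% test on individuals, no clustering, and **no true effect of support on anyone**.

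**2. Proportion showing a change.** Let q be the share of enrolled people inactive at baseline, a the chance of a change if inactive, and b the chance if already active. The expected proportion is p = q·a + (1 − q)·b, so the spurious difference is (q_IG − q_CG)·(a − b). With q_CG = 0.60:

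| a, b | q_IG | p_CG | p_IG | Spurious difference | Chance the test rejects |
|---|---|---|---|---|---|
| 0.30, 0.10 | 0.70 | 0.220 | 0.240 | +0.020 | 0.07 |
| 0.30, 0.10 | 0.80 | 0.220 | 0.260 | +0.040 | 0.14 |
| 0.40, 0.05 | 0.70 | 0.260 | 0.295 | +0.035 | 0.11 |
| 0.40, 0.05 | 0.80 | 0.260 | 0.330 | +0.070 | 0.31 |
| 0.40, 0.05 | 0.50 | 0.260 | 0.225 | −0.035 | 0.12 |
| 0.30, 0.10 | 0.50 | 0.220 | 0.200 | −0.020 | 0.07 |

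If q is equal in both arms, the difference is 0 and the test rejects at its nominal 5%.

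**3. Change scores.** Suppose baseline means differ by s standard deviations through selection, the baseline-to-post correlation is r, and both groups regress toward a common mean. The spurious difference in change is s(1 − r), and the standard deviation of change is √(2(1 − r)).

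| r | s | Spurious difference (SD) | Chance the test rejects |
|---|---|---|---|
| 0.7 | 0.1 | 0.03 | 0.06 |
| 0.5 | 0.3 | 0.15 | 0.30 |
| 0.3 | 0.5 | 0.35 | 0.80 |

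Analyzing changes instead of levels does not remove the bias, and neither does a larger sample.

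The article says effectiveness is analyzed by professional. The spurious differences do not depend on that choice. The rejection rates do, so they show only that the bias could matter.

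**4. What adjustment does.** In step 2, compare within baseline-activity strata: inactive people show a against a, active people b against b, and the adjusted difference is 0. In step 3, adjusting for baseline likewise gives 0 under the stated model.

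**5. What adjustment cannot do.** Let the selecting factor be motivation, which the article does not list among the screening criteria. Assume motivated people change in 60% and others in 20%. With 50% motivated in control: 0.5 × 0.6 + 0.5 × 0.2 = 0.40. With 30% in the intervention arm: 0.3 × 0.6 + 0.7 × 0.2 = 0.32. With 70%: 0.7 × 0.6 + 0.3 × 0.2 = 0.48. If motivation is unrelated to the adjustment variables, the −8 or +8 points remain.

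**The case against.** The best counter-argument is that the trial tests an implementation strategy of which recruitment is a part. On that view, any influence on who enrolls belongs to the effect of the package, and Reach, including representativeness, is reported beside Effectiveness. This stands in part: the Reach comparison is sound, because enrollment is the outcome there. But change among enrollees is not the package effect on the population served, since it leaves out everyone not enrolled. Nor is it the effect on comparable people.

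Several stronger readings are tempting, and the documents do not support them:

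- *Control providers get only posters.* They also have the common training and teaching materials with recruitment content, and the criteria, questionnaire and screening meeting are set out without distinction of arm.
- *Intervention providers are told to enroll a different kind of person.* In Table 1, 'who' may mean who does the recruiting; the evaluation row of the same table speaks of the professionals involved. An altered case mix is a plausible risk, not a stated aim. The remaining guidelines, the goals and the staged messages still differ between arms.
- *The comparison cannot show anything about support.* That is too absolute. The bias may be small, and adjustment can reduce it.
- *Effectiveness should become changers per exposed user.* That counts unmeasured non-enrolled users as non-changers and merges Reach into Effectiveness. Its denominator also depends on an announcement period that is only recommended.

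The planned tests of group characteristics can reveal an imbalance but do not correct it. A fuller analysis plan, not shown, may add adjustment. The point here is that the article itself names an unadjusted test and reads the result as the impact of the strategies.

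**Conclusion.** The concern holds in this form: enrollment follows allocation, recruitment support differs by design on top of a shared base, and the stated unadjusted comparison among enrollees can mix the effect of support on behavior with differences in who was enrolled. Facility randomization does not prevent this.

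The documents fix neither size nor direction. The range of 2 to 7 points, with about 7% to 31% false rejection, rests on assumed change rates and an assumed rise of 10 to 20 points in the share of inactive enrollees. The range of 0.03 to 0.35 SD, with about 6% to 80%, rests on assumed baseline shifts of 0.1 to 0.5 SD and correlations of 0.3 to 0.7. A reader might infer that the trial will report support as harmful, or as beneficial, when it is not. Either is possible under suitable assumptions, and the article supports neither as a prediction.

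**What to change.** In the Effectiveness text and in Data analysis, replace the unadjusted between-arm test with a comparison adjusted for the baseline value of the outcome and a short, prespecified list of screening characteristics, in an analysis that respects the facility as the unit of allocation. Age, weight status and chronic disease are part of the eligibility check. Sex is a natural addition; the article does not name it, so its place on the questionnaire should be confirmed.

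State that the result compares enrolled groups and that unmeasured selection, such as motivation, may remain. Interpret it together with the between-arm Reach rates and the baseline characteristics by arm.

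Changers per exposed user may be added as a supplementary measure combining reach and effectiveness, provided the announcement window is the same in both arms. It should not replace the effectiveness outcome. Table 2 lists interested, enrolled, retained and dropout counts for Reach, so the exposed count needed for this measure, and for the recruitment rate, should be named there.

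The cost is slightly more analysis and a more cautious causal claim. The core change should need no new participant data, apart from the point on sex.
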